The exit standard for the trial indicates that subjects can drop out of the experiment at any time for the following reasons: the subjects withdraw their informed consent; the subjects are lost to follow-up; and the subjects ask to stop or change the medicine. During the study, when the subjects meet the above termination/withdrawal criteria, the researchers can terminate the participation of the subjects and continue the follow-up treatment and follow-up as far as possible according to the medical routine. The reason and date of the subject's withdrawal must be recorded in the case report form and the original data.

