**Enrollment and follow-up**

Those who meet the enrollment criteria will enter the intervention:

On the 3rd day of enrollment, the following procedures will be performed: (1) record concomitant medication; (2) record adverse events; and (3) carry out CT examination.

On the 7th day (±1 day)), the following procedures will occur: (1) record the combined use of drugs; (2) record adverse events; (3) measure vital signs: respiratory rate, heart rate and blood pressure; (4) evaluate clinical symptoms: dyspnea score; (5) perform routine laboratory examination: routine blood, routine urine, liver and kidney function, blood glucose, electrolyte, troponin, hypersensitive CRP, procalcitonin, serum ferritin; (6) assess inflammation index (CRP, IL-6, TNF- α), infection index (routine blood tests, PCT) and immune function (T cell subsets); (7) analyze arterial blood gas: pH, PaO2, PaCO2 and oxygenation index; (8) perform HRCT examination and score; and (9) calculate APACHE II score.

Fourteen days after admission (±3 days) or discharge, (1) record the combined use of drugs; (2) monitor possible adverse reactions to ixekizumab; (3) check vital signs: respiratory rate, heart rate, blood pressure; (4) evaluate clinical symptom: dyspnea score; (5) perform routine laboratory examination: routine blood, routine urine, liver and kidney function, blood glucose, electrolyte, troponin, hypersensitive CRP, procalcitonin, serum ferritin; (6) assess inflammation index (CRP, IL-6, TNF-α), infection index (routine blood, PCT) and immune function (T cell subsets), and so on; (7) analyze arterial blood gas: pH, PaO2, PaCO2 and oxygenation index; and (8) perform HRCT examination and score; (9) APACHE Ⅱ score was calculated (Figure 1).

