**Treatment Protocols**

After the subjects sign the informed consent form, the researchers will complete the evaluation within 2 days.

The first phase: open design. Three subjects are enrolled in the same center. They are given ixekizumab and antiviral therapy (aerosol inhalation of α-interferon, lopinavir/ritonavir, chloroquine, ribavirin, or arbidol but not more than 3 types). The vital signs and changes in disease, inflammation indexes (CRP, IL-6, TNF-α) and infection indexes (routine blood tests) are monitored. Changes in PCT and immune function (T cell subsets) are detected. If there are no serious drug-related safety events in the patient's condition, the results of the first stage will be reported to the ethics committee for evaluation and approval, and the second phase of the study will be carried out.

In the second stage, 40 subjects are randomly divided into two groups at a 1:1 ratio. They are given ixekizumab and antiviral therapy (aerosol inhalation of α-interferon, lopinavir/ritonavir, chloroquine, ribavirin, or arbidol but not more than 3 types) or antiviral therapy alone. The course of treatment is 14 days. The vital signs, blood oxygen saturation, CT and other related indexes are followed up on days 0, 3, 7, and 14. The changes in inflammation indexes (CRP, IL-6, TNF-α), infection indexes (blood routine, PCT) and immune function (T cell subsets) and other indexes are monitored. The last follow-up is completed on the 14th day or early recovery and discharge (Figure 2).

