**Secondary outcomes**

1) Pulmonary function prognostic indicators: percentage of subjects reporting each severity level (on a 7-point scale) (https://clinicaltrials.gov/ct2/show/NCT04280705). The scale is the assessment of clinical status at the first evaluation on a specified study day. The indicators are as follows: (1) death; (2) admission due to invasive mechanical ventilation or extracorporeal membrane oxygenation (ECMO); (3) hospitalization with noninvasive ventilation or high-flow oxygen equipment; (4) hospitalization requiring oxygen inhalation; (5) hospitalization without oxygen inhalation; (6) hospital discharge with limited activity; and (7) no need to be hospitalized and activities are not restricted.

2) Clinical symptom relief time: Clinical symptom relief is defined as normal body temperature for >72 hours (without taking antipyretic drugs or glucocorticoids) and no conscious dyspnea or relief of dyspnea.

3) The incidence of admission to the ICU on the 3rd day, 7th day and 14th day;

4) The incidence of noninvasive ventilation on the 3rd, 7th and 14th days;

5) 14-day etiological mortality and 14-day all-cause mortality;

6) Length of hospitalization;

7) Changes in troponin, inflammation indexes (CRP, IL-6, TNF-α), infection indexes (blood routine, PCT) and immune function (T cell subsets)) on the 7th and 14th days.

8) The ratio of arterial partial pressure of oxygen (PaO2) to fraction of oxygen inhalation (FiO2) on the 3rd, 7th and 14th days.

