**Statistical analysis plan**

**Sample Size Projections**

Forty-three cases were planned to be included in the group. Sample size estimation: This study is an open exploratory study, so the sample size is not statistically estimated. According to the estimation of clinical researchers, 43 cases are planned to be included in the group.

The statistical analysis in this study will be performed using SAS software. The statistical description of the quantitative variable calculates the mean, standard deviation, median, 25% quantile Q1, 75% quantile Q3, minimum and maximum.

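### Three secondary outcomes (ICU admission, noninvasive ventilation, length of stay) take no account of death or, for noninvasive ventilation, direct intubation, and stays beyond the last visit are not observed

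*Protocol*

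**What the plan says.** All three outcomes stand in the Protocol under Secondary outcomes:

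- Outcome 3: "3) The incidence of admission to the ICU on the 3rd day, 7th day and 14th day".
- Outcome 4: "4) The incidence of noninvasive ventilation on the 3rd, 7th and 14th days".
- Outcome 6: "6) Length of hospitalization", with no start, end or further definition.

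The same list also holds "5) 14-day etiological mortality and 14-day all-cause mortality" and a 7-point clinical status scale. On that scale death is level 1, invasive ventilation or ECMO is level 2, and noninvasive ventilation or high-flow oxygen is level 3.

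Two places set the length of observation. Treatment Protocols says "The last follow-up is completed on the 14th day or early recovery and discharge (Figure 2"). Enrollment and follow-up puts the last visit at "Fourteen days after admission (±3 days) or discharge". After termination or withdrawal, the investigators are to "continue the follow-up treatment and follow-up as far as possible according to the medical routine", but no contact after the last visit is scheduled.

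**The concern.** The Eligibility Criteria exclude patients who already need mechanical ventilation and admit severe and high-risk cases. Intubation and death are therefore events after entry that the outcomes should register as bad.

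The three definitions look at one event each and pass over the worse events that can prevent it or end it early. A patient who dies early can no longer be ventilated noninvasively, can no longer be admitted to the ICU, and has a short stay. A patient intubated without a prior trial of noninvasive ventilation never has the outcome 4 event. Outcome 4 therefore runs against the severity ordering of the protocol's own 7-point scale.

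An arm with more early deaths could then show a lower incidence on outcomes 3 and 4 and a shorter stay on outcome 6. The interim review under Interim analysis covers efficacy and safety, so such figures could also reach the monitoring board.

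**Working it through.** The protocol gives no event rates or lengths of stay and no statistical basis for its sample size. There is no figure of its own to reproduce beyond 3 + 40 = 43 patients. The definitions are checked by reading, and their effect is illustrated with assumed values.

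**1. Each course against each definition**

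| Course after entry | Outcome 3 (ICU) | Outcome 4 (noninvasive ventilation) | Outcome 6 (stay) |
|---|---|---|---|
| Death without ICU admission or noninvasive ventilation | non-event | non-event | shortened |
| Direct intubation | normally an ICU admission, so counted | non-event | normally longer |
| Noninvasive ventilation, then intubation or death | depends on ICU admission | counted if incidence is cumulative; can be missed if it is status on the day | shortened only by death |

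The protocol does not say whether incidence on days 3, 7 and 14 is cumulative or status on the day. The first row holds under both readings. Under status on the day, a patient on noninvasive ventilation on day 5 who is intubated or dead by day 7 also reads as no event at day 7.

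**2. Size for outcome 4**

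From the protocol: 40 patients at 1:1, so 20 per arm, and one patient is 1/20 = 5 percentage points. Assumed: 30% of an arm need ventilatory support or die, and a fraction *f* of these go straight to intubation or death. Recorded incidence = 0.30 × (1 − *f*).

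- *f* = 0: 30% (6 of 20)
- *f* = 0.25: 22.5% (4.5 of 20 expected)
- *f* = 0.50: 15% (3 of 20)

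The arm with the worse course has the lower figure.

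**3. Size for outcome 6, effect of death**

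Simple case, 20 patients: all stay 14 days, or 18 stay 14 days and 2 die on day 4. The mean is 14.0 in the first and (18×14 + 2×4)/20 = 260/20 = 13.0 days in the second. The median is 14 in both.

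Spread-out stays: assume lognormal, median 14 days, log SD 0.45. The mean is 14 × exp(0.45²/2) = 15.49 days. Suppose a share *q* die on day 7 unless already discharged. The average stay of that share is E[min(stay, 7)] = 6.93 days, so the arm mean is (1 − *q*) × 15.49 + *q* × 6.93.

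- *q* = 5%: 15.1 days
- *q* = 10%: 14.6 days
- *q* = 20%: 13.8 days

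**4. Size for outcome 6, end of observation**

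With the same log SD, the share of stays beyond day 14 is 1 − Φ(ln(14/median)/0.45).

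- median 10 days: 23%
- median 14 days: 50%
- median 18 days: 71%

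For medians of 18 and 14 days, the true difference in means is 19.92 − 15.49 = 4.4 days. If unobserved stays were entered as 14 days, it would shrink to 13.08 − 12.06 = 1.0 day. If entered as 17 days, it would be 14.98 − 13.29 = 1.7 days.

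**5. Check of the remedy on the simple case**

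If the survivors go home on day 14, the proportion discharged alive by day 14 is 20/20 = 100% without deaths and 18/20 = 90% with the two deaths. The direction is now right. If the two deaths were instead censored at day 4, the Kaplan–Meier estimate would reach 100% in both cases and the difference would vanish. That is why death must be a competing event.

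**The case against.** **No rule in the protocol scores death or intubation as a good result.** This is correct. A reader might infer such a rule, but the effect follows only from bare definitions. An analysis plan that is not shown may say how death and patients still in hospital are handled. Two things remain. What counts as an event is fixed by the protocol. And no analysis plan can supply discharge dates that nobody is scheduled to collect after the last visit.

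**Faster intubation would not look good on all three outcomes.** Also correct. Nothing in the protocol makes intubation avoid ICU admission or shorten the stay; ordinarily it does the opposite. Direct intubation affects outcome 4 only.

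**The protocol does not cut length of stay at day 14.** Correct. The limit is inferred from the end of follow-up, and the visit window reaches day 17. What stands is that longer stays are not observed and the protocol gives no rule for them.

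**The harm is visible elsewhere.** This carries most weight. All-cause mortality at 14 days, levels 1 and 2 of the 7-point scale and the comparison of adverse events between groups would show excess deaths or intubations. A claim that harm is hidden is not supported.

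**The mean need not be the analysis of stay.** The general sentence that begins "The statistical description of the quantitative variable calculates the mean, standard deviation" goes on to list the median and quartiles. In the simple case above the median does not move. The one-day shift is a property of the mean under assumed values.

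**Deaths also leave no later CT score.** A reader might extend the point to the primary outcome. That is a separate missing-data question, which an analysis plan commonly settles, and it is not part of this point.

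**Conclusion.** The point holds in a limited form. Death is not accounted for in outcomes 3, 4 and 6, direct intubation is not accounted for in outcome 4, and stays beyond the last visit are not observed. The direction is certain from the definitions: these events can make an arm look better on those outcomes.

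The size depends on assumptions the protocol does not supply. In the illustrations, noninvasive ventilation incidence reads 15% to 22.5% instead of 30%, mean stay falls by 0.4 to 1.7 days for 5% to 20% early deaths, and 23% to 71% of stays run past day 14. The lognormal shape, its spread and the event rates are all assumed.

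The consequence is misleading secondary results in a small exploratory trial, not concealed harm. The primary outcome is untouched by this point. It is a worthwhile, cheap improvement.

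**What to change.** - **Outcome 4:** noninvasive ventilation, invasive ventilation/ECMO or death, cumulative by days 3, 7 and 14.
- **Outcome 3:** ICU admission or death, cumulative by the same days.
- For both, list each component separately beside the composite. Use dates of ventilation, ICU admission and death from the hospital record. The 7-point scale alone will not do, because it gives status on specified days and not events in between.
- **Outcome 6:** time to discharge alive through day 14. Treat death as never discharged, that is, as a competing event and not censored at death. Censor patients still in hospital at the last visit. Name the time origin, because the last visit is counted from admission in one section while other sections count study days from day 0.

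Days alive and out of hospital with death set to 0 is not a good substitute. It gives 0 both to a death and to a survivor still in hospital at day 14, and it needs status after discharge, which follow-up does not cover.

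The cost is protocol wording, programming and recording event dates during the stay; no visit is added. The composites are less specific than their components, which is why the components stay listed.

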**Security assessment**

**Safety index**

The incidence of adverse events/serious adverse events; laboratory examination (blood routine, blood biochemistry, urine routine), vital signs, physical examination and electrocardiogram before and after treatment.

**Report and follow-up of adverse events and serious adverse events.**

Adverse events and serious adverse events should be diagnosed clinically as much as possible, and symptoms and signs can only be used if the diagnosis is unknown. Diagnostic terms can be referred to the WHO glossary. In the case of bacterial or fungal infection, active treatment will be given according to clinical routine and novel coronavirus diagnosis and treatment and followed up until cured or stable.

**Data Collection and Data Management**

In this study, the team of researchers is responsible for data management to ensure the authenticity, integrity, privacy and traceability of the clinical trial data. Two people will enter clinical data into the Epidata3.0 database. This study adopts the method of manual verification, and professional statisticians are invited to verify the data if necessary. After the data are entered into the database, if there are any illogical data, it will trigger doubt. These questions need to be reviewed and answered by the researcher or a person authorized by the researcher. Before locking the database, the data administrator should ensure that all queries have been resolved to ensure the completeness and accuracy of the subjects' data. Past medical history and adverse events will be coded according to the MedDRA dictionary, and accompanying medication will be coded using the World Health Organization Drug Dictionary (WHO DD), all of which are in a recognized version.

**Statistical analysis plan**

**Sample Size Projections**

Forty-three cases were planned to be included in the group. Sample size estimation: This study is an open exploratory study, so the sample size is not statistically estimated. According to the estimation of clinical researchers, 43 cases are planned to be included in the group.

The statistical analysis in this study will be performed using SAS software. The statistical description of the quantitative variable calculates the mean, standard deviation, median, 25% quantile Q1, 75% quantile Q3, minimum and maximum.

**Subject distribution**

The screening of the subjects, joining of the groups, completion of the study and reasons for the failure of screening, reasons for early withdrawal, and so on will be summarized and described. The case distribution of each data set, elimination of each analysis set and reasons for elimination, as well as violations of at least one important scheme, will be summarized and described.

**Demographic data and baseline characteristics**

Demographics and baselines will be analyzed in the FAS set and the PPS population. All demographic variables and baseline characteristics (such as age, sex, height, weight, past diseases, past medication, past treatment history, vital signs, etc.) will be summarized. Descriptive statistics (number of subjects, average, standard deviation, minimum, Q1, median, Q3 and maximum) will be used as continuous variables, and classified variables will be used to calculate frequency and percentage ratio.

**Analysis of curative effect**

For the subjects who participated in the study, the FAS set and PPS set will be used to analyze the effectiveness, in which the PPS set is the main analysis set of efficacy analyses.

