**Eligibility Criteria**

The inclusion criteria for the trial are as follows: the age is 18-75 years old, regardless of sex; COVID-19 will be diagnosed by RT-PCR or gene sequencing; the clinical types are common type (including severe high-risk factors) (multiple lesions of both lungs, or lung imaging showing that the lesion progressed more than 50% within 24 to 48 hours) and severe type; an increase in IL-6 levels; and the patient voluntarily signing the informed consent form.

The exclusion criteria for the trial are as follows: severe new pneumonia infection with one of the following conditions: respiratory failure requiring mechanical ventilation, shock, ICU monitoring and treatment with other organ failure; allergy to ixekizumab or antiviral drugs; ALT/AST>5 times the ULN, neutrophils<0.5 × 10^9/^L, or platelet less than 50 × 10^9^/L; patients with impaired renal function: serum creatinine ≥2 mg/dl (176 μmol/l); complications with severe underlying diseases or a life expectancy of less than 3 months; patients with active hepatitis, definite severe bacterial or fungal infections, tuberculosis infection, or HIV infection; malignant tumors, such as lymphoproliferative diseases; active Crohn's disease; pregnant or lactating women; participation in other intervention clinical trials in the past 3 months; or other situations in which the researchers believe that it is not appropriate to join the group.

The termination standards for the trial are as follows: allergy to research drugs; judgment of the researchers that it is necessary to terminate the study ahead of time because continuing to participate in the study may bring unacceptable risks to the subjects' health based on the occurrence of serious adverse events, or the subjects are unwilling to continue to participate in the study because of the adverse events; the observation of the curative effect was affected by other diseases such as stroke in the trial; or the ethics committee or regulatory body requested that the study be suspended.

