**Prohibited combinations**

Other drugs that regulate the storm of immune factors, such as IL-6R monoclonal antibodies or TNF-α inhibitors, may not be used. It should also not be used at the same time as live vaccines.

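### The per-protocol set is named the main efficacy set for the randomised comparison, which leaves the main result open to bias from post-randomisation exclusions

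*Protocol*

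**What the plan says.** Under Analysis of curative effect, the Protocol states that "the FAS set and PPS set will be used to analyze the effectiveness", and ranks the two sets: "in which the PPS set is the main analysis set of efficacy analyses".

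The comparison is set out under Treatment Protocols: "In the second stage, 40 subjects are randomly divided into two groups at a 1:1 ratio". One group receives ixekizumab with antiviral therapy, the other "or antiviral therapy alone". The primary outcome is the change in pulmonary CT score, read by blinded third-party experts. Sample Size Projections calls the study open and exploratory.

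The Protocol defines neither set. It does list events after enrolment that end or disturb participation:

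- Eligibility Criteria, termination standards: allergy to the research drugs, adverse events, or "the observation of the curative effect was affected by other diseases such as stroke in the trial".
- Eligibility Criteria, exit standard: withdrawal of consent, loss to follow-up, or "the subjects ask to stop or change the medicine".
- Prohibited combinations: other drugs acting on the cytokine storm, "such as IL-6R monoclonal antibodies or TNF-α inhibitors, may not be used".

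Subject distribution expects some patients to be eliminated from the analysis sets and asks for the reasons to be summarised.

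**The concern.** Stage 2 asks whether adding ixekizumab to antivirals helps. The Protocol does not use the word superiority, but an add-on design with no equivalence or non-inferiority aim or margin implies it. The usual reason to give weight to a per-protocol set, that the full set can hide a difference when the aim is to show similarity, does not apply.

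Randomisation makes the two groups of 20 comparable as allocated. A per-protocol set keeps only patients to whom certain things did not happen afterwards. If those things depend on treatment or on how ill the patient became, the retained groups need no longer be comparable. An ixekizumab allergy can occur in one arm only. A stroke, or a prohibited agent given to a deteriorating patient, is linked to prognosis. In an open study, a request to stop or change medicine can depend on knowing the allocation. Blinded CT reading protects how the score is measured, not which patients are analysed.

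At stake is the headline efficacy result. With 20 per arm, each excluded patient is 1/20 = 5% of an arm. The Protocol itself fixes which set prevails, so a separate analysis plan that follows it would inherit the choice.

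**Working it through.** **What can be reproduced.** The Protocol gives no significance level, power, effect size, SD or expected exclusion rate. Its only figure is the planned total ("43 cases are planned to be included in the group"), and 3 + 40 = 43 agrees with the two stages. Everything below is illustration under stated assumptions.

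**Inputs from the Protocol.** 40 randomised 1:1, so 20 per arm; a quantitative primary outcome; the PPS as main set.

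**Assumptions.** No true effect; outcome normal with SD 1, higher meaning worse; two-sided t-test at 5%; patients removed from the worst end of a ranking whose correlation with the outcome is ρ; 4 of 20 removed in one arm and 1 of 20 in the other.

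**Bias at ρ = 1.** The expected values of the four largest of 20 standard normal observations are about 1.87, 1.41, 1.13 and 0.92, which sum to 5.33.

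- Arm losing its worst 4: the mean of the remaining 16 is −5.33/16 = −0.333.
- Arm losing its worst 1: the mean of the remaining 19 is −1.87/19 = −0.098.
- Spurious difference: 0.333 − 0.098 = 0.235 SD, in favour of the arm that lost more patients.

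**Bias at other ρ.** The bias is ρ × 0.235: 0.07 at ρ = 0.3, 0.12 at ρ = 0.5, and 0 at ρ = 0.

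**Type I error, by simulation (4 v 1 removed).**

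| ρ | Bias (SD) | Type I error |
|---|---|---|
| 0 | 0 | about 5% |
| 0.3 | 0.07 | about 5.5% |
| 0.5 | 0.12 | about 6.7% |
| 1 | 0.235 | about 15% |

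Repeat runs of the middle rows gave up to 5.8% and 6.9%.

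**How to read the last row.** Part of the 15% is not arm imbalance. Removing exactly the worst 4 from both arms gives no bias but still about 10% type I error, because cutting off one tail shrinks the observed SD.

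**Lighter imbalance (3 v 1).** 0.16 SD and about 11% at ρ = 1; about 6.2% at ρ = 0.5; about 5.3% at ρ = 0.3.

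**Direction.** If the larger loss of poor-prognosis patients is in the ixekizumab arm, the bias favours ixekizumab. If it is in the control arm, the same figures apply against ixekizumab. The Protocol does not allow one to say which is more likely.

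**The case against.** The strongest defence is that the trial is a pilot and calls itself open and exploratory, has no calculated sample size, and reads its primary outcome blind. It also analyses the FAS and reports eliminations with their reasons, so a reader can compare the two sets. All of this is true and lowers the stakes. It does not answer the point, because the plan says which result is the main one if the two differ. The Conclusion also expects the results to help clinicians and policy makers develop treatment plans.

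Other objections limit what can be claimed, and they stand:

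- **Reasons for leaving the PPS.** The set is undefined, so the listed events are possible reasons for exclusion, not stated ones. Allergy to research drugs might also cover antivirals, in either arm. A reader might infer that controls would receive prohibited agents more often; nothing in the Protocol supports that.
- **Adherence.** It is tempting to say that a single injection leaves a per-protocol set nothing to do. But both arms also receive antivirals over a 14-day course, where non-adherence is possible.
- **Stage 1.** The efficacy section speaks of subjects who took part, and the planned total is 43, so a reader might infer that the three open-label patients join the ixekizumab group. The Protocol does not say so. The 43 is planned enrolment. Study Design, Treatment Protocols and Figure 2 keep the stages apart, with ethics review between them and randomisation in stage 2 only.
- **Follow-up.** The exit standard already continues follow-up as far as routine care allows. What it lacks is an explicit commitment to the scheduled outcome assessments.

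**Conclusion.** The choice of main set is wrong as written and should be changed. The Protocol makes the PPS the main efficacy set of a randomised add-on comparison with no stated aim that would justify it. That opens the main result to selection after randomisation, in either direction.

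The size is unknown because the exclusions are unknown. With 4 v 1 removals and ρ between 0.3 and 0.5, the illustration gives 0.07 to 0.12 SD of bias and a type I error slightly above 5%. It reaches 0.235 SD and 15% only if patients are removed strictly in order of outcome, and 15% should not be quoted as the expected error rate. The error rates also assume a 5% test, which the Protocol does not state.

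A reader might go further and call the result biased, or the protection of randomisation lost. The documents do not support that: if exclusions are unrelated to outcome the bias is zero, and the FAS analysis remains as a check. The accurate statement is that the main result is open to bias.

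**What to change.** In Analysis of curative effect, make the FAS the main efficacy set, defined as all stage-2 randomised patients analysed in the arm to which they were randomised, and keep the PPS as a supportive analysis.

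In the exit standard, add that after termination or exit the scheduled Day 7 and Day 14 outcomes are still collected unless the patient withdraws consent to data collection. Without this, a full analysis set would be complete in name only.

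The cost is about one sentence in each place, with no change to treatment or sample size. The downside is that the estimate may be slightly diluted by patients who change treatment; the supportive PPS analysis can show how much the result depends on them.
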